### Adverse events

During the study, all adverse events, including toxicity and side effects, such as drug allergies, liver damage, renal failure, bone marrow suppression, and pancreatitis, will be reported and recorded in the case report form in detail. The researcher will report serious adverse events to the Institutional Review Board of Human Research of the Affiliated Hospital of Nanjing University of Chinese Medicine.

### Data management and statistical analysis

Data recorded in printed case report forms are kept in locked cabinets. Data will be double-entered on electronic case report forms by two persons. Frequency, median, and mean ± standard deviation of the steroid-free remission rate and the mean withdrawal time of steroids will be used for descriptive statistics. Student’s *t* test and analysis of variance will be employed using continuous variables with a normal distribution. The Mann–Whitney *U* test and Kruskal–Wallis test will be used for continuous variables with abnormal distributions, such as health-related quality of life and inflammation markers. A chi-square test or Fisher’s exact test will be used for categorical variables, including the efficacy of endoscopic response and the degree of mucosal healing. Results will be analyzed as per intention-to-treat. All data will be analyzed by an independent statistician using SAS 9.4. For all analyses, *P* < 0.05 is considered statistically significant.

To summarize the present study protocol, please see Additional file 1 for an overview of enrollment, interventions and assessments, and Additional file 2 for an overview of the Standard Protocol Items: Recommendations for Interventional Trials (SPIRIT) checklist.

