### Sample size

The remission rate for ulcerative colitis by azathioprine ranges from 59.1% to 87% [9, 10], and the average rate is about 73%. This is a noninferiority trial. For a two-sided significance level of 0.05 and power of 80% (*α* = 0.05, *β* = 0.2, *δ* = 0.15), the sample size is calculated using the formula:$$ n=12.365\times P\left(1-P\right)/{\delta}^2 $$

Considering a 10% loss to follow-up, the sample size is 120 cases (*n* = 60 in each group).

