### Interventions

#### Basic treatment

All eligible steroid-dependent patients will continue their initial steroid and 5-aminosalicylic therapy. Withdrawal of steroids occurs along with clinical remission. If there is clinical remission, a taper dose will be initiated with 5 mg taper weekly until a 20 mg daily dose is reached. Then tapering should proceed by 2.5 mg per week [11].

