#### Secondary outcome measures

The key secondary aim is to investigate the effect of Chinese herbal medicine granules on health-related quality of life in steroid-dependent patients compared with azathioprine, as measured by the inflammatory bowel disease questionnaire. Other secondary outcome measures include the efficacy of endoscopic response, which is defined as a decrease from baseline in a Mayo disease activity index endoscopy subscore by at least 1 [14]. The degree of mucosal healing is defined as a Mayo disease activity index endoscopy subscore of 0 or 1 [15]. Improvements in inflammation indicators include fecal calprotectin, C reactive protein, and erythrocyte sedimentation rate.

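### Quality of life, inflammation markers and endoscopic outcomes are assigned tests with no baseline covariate, which costs precision but not validity

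*Protocol article*

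**What the plan says.** The section on data management and statistical analysis chooses tests by type of variable:

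- t test and analysis of variance for normally distributed continuous variables.
- Mann–Whitney and Kruskal–Wallis "for continuous variables with abnormal distributions, such as health-related quality of life and inflammation markers".
- Chi-square or Fisher's exact test for categorical variables, with endoscopic response and mucosal healing as the named examples.

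No ANCOVA, regression model, stratified test or covariate appears there. The Randomization section mentions no stratification.

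Under Secondary outcome measures, endoscopic response is a fall of one point or more in the Mayo endoscopy subscore relative to baseline. For the laboratory markers the text reads "Improvements in inflammation indicators include fecal calprotectin, C reactive protein, and erythrocyte sedimentation rate". The quality-of-life questionnaire is the key secondary outcome, and nothing is said about its baseline.

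Under Basic treatment, patients enter on their own steroid dose. At clinical remission "a taper dose will be initiated with 5 mg taper weekly until a 20 mg daily dose is reached", and weekly steps of 2.5 mg follow. The primary outcome, steroid-free remission, is assessed at 24 weeks. If the two rates do not differ significantly, mean steroid withdrawal time is compared. The Sample size section says "This is a noninferiority trial", with a margin of 0.15 and 60 patients per group.

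**The concern.** The follow-up level of a questionnaire score or an inflammation marker usually tracks its baseline level. A comparison that ignores baseline leaves that between-patient variation in the standard error. With 60 patients per group this matters most for the key secondary outcome and the markers.

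The endoscopic outcomes depend on baseline through their definitions. A patient who enters with a subscore of 0 cannot show a one-point fall, and one who enters at 0 or 1 already meets the definition of mucosal healing. The eligibility criteria as printed set no minimum subscore.

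Withdrawal time contains the taper, and the length of the taper is set by the entry dose. Variation in entry dose therefore goes straight into that comparison as noise.

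**Working it through.** **1. The plan's own sample-size figure.** Inputs from the Sample size section: P = 0.73, δ = 0.15, constant 12.365, 10% loss.

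- 12.365 × 0.73 × 0.27 / 0.15² = 108.3, and 108.3 / 0.9 = 120.4. The stated 120 is reproduced if 108 is taken as the total.
- But 12.365 = 2(z₀.₉₅ + z₀.₈₀)², so the formula gives the number per arm, at one-sided 0.05.
- The plan leaves 60 × 0.9 = 54 evaluable per arm. Power = Φ(δ / √(2P(1−P)/n) − z₁₋α). The standard error is √(2 × 0.1971 / 54) = 0.0854, and 0.15 / 0.0854 = 1.756.
- Power is 54.4% at one-sided 0.05 and 41.9% at one-sided 0.025 (the counterpart of two-sided 0.05).

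**2. Continuous secondary outcomes.** The correlation r between baseline and week 24 is not in the document, so 0.3 to 0.7 is assumed. ANCOVA variance relative to week-24 values is 1 − r². Relative to change scores it is (1 − r²) / (2(1 − r)) = (1 + r)/2.

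| r | Cut against week-24 values | 54 per arm is worth | Cut against change scores |
|---|---|---|---|
| 0.3 | 1 − 0.91 = 9% | 54/0.91 = 59 | 1 − 0.65 = 35% |
| 0.5 | 1 − 0.75 = 25% | 54/0.75 = 72 | 1 − 0.75 = 25% |
| 0.7 | 1 − 0.51 = 49% | 54/0.51 = 106 | 1 − 0.85 = 15% |

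At an assumed standardized difference of 0.5 with 54 per arm, power on week-24 values is 73.8%. With ANCOVA it is 77.7%, 85.1% and 95.3% at the three correlations. With change scores it is 59.3%, 73.8% and 91.8%. The article does not say whether values or changes are tested. ANCOVA is more precise than either across this range.

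**3. Taper and entry dose.** Taper weeks = (dose − 20)/5 + 20/2.5 above 20 mg, and dose/2.5 at or below 20 mg. The document gives no range of entry doses, so those below are illustrative. Applying the 2.5 mg step to patients who enter at or below 20 mg is an inference.

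| Entry dose | Taper | Latest start to finish by week 24 |
|---|---|---|
| 10 mg | 4 weeks | week 20 |
| 20 mg | 8 weeks | week 16 |
| 40 mg | 4 + 8 = 12 weeks | week 12 |
| 60 mg | 8 + 8 = 16 weeks | week 8 |

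These figures assume an uninterrupted taper. Withdrawal time depends directly on entry dose.

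**4. What this is worth for the primary outcome.** An illustrative model assumed exponential time to remission with mean 4 or 8 weeks, entry doses spread evenly over 10–40 mg or 20–60 mg, and 10% failing for other reasons. Entry dose then explained 0.2% to 3.1% of the variance of steroid-free remission. Multiplying the variance in step 1 by (1 − R²) at R² = 0.03 moves power from 54.4% to 55.5% (one-sided 0.05), or from 41.9% to 43.0% (one-sided 0.025). To reach 80% the covariates would need R² = 0.50 or 0.61.

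**The case against.** Four points can be made on the other side.

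- **The tests are valid.** Randomization protects the type I error of unadjusted comparisons, and chance imbalance is already reflected in their standard error. This stands. A reader might infer that an imbalance in entry dose would bias the result or inflate its error rate. Nothing in the design supports that.
- **The list may be generic, with covariates left to an SAP that is not shown.** For the primary outcome this has force. The analysis section mentions steroid-free remission only under descriptive statistics, and chi-square follows only from its being categorical. It has less force for quality of life, the markers and the endoscopic outcomes, which are each matched to a test that takes no covariate.
- **Baseline collection is partly inferred.** This stands. It is explicit for the endoscopy subscore and implied for the markers by the word for improvement. For the questionnaire and entry dose it is only plausible, although the taper cannot be run without knowing the dose. The assessment schedule is in Additional file 1, which is not shown.
- **The correlations are assumed, and the comparator is a difference in means rather than the planned rank test.** This also stands. On skewed markers the percentages guide the gain on the log scale and do not measure the gain over Mann–Whitney exactly. A Hodges–Lehmann shift with an interval could accompany the rank test, but it would not be adjusted for baseline.

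**Conclusion.** The point holds as one of efficiency, mainly for secondary outcomes. For quality of life and the three markers, baseline adjustment would remove 9% to 49% of the variance of a week-24 comparison, or 35% to 15% of that of a change-score comparison, for assumed correlations from 0.3 to 0.7. The endoscopic outcomes and withdrawal time also depend on baseline, through their definitions and through the taper, but the document gives no data to size that gain.

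A reader might go further and infer that, because the taper ties steroid-free remission to entry dose, adjustment would rescue an underpowered primary analysis. The figures do not support this. Entry dose is worth about 1 point of power in the illustrative model. Baseline Mayo score may add something, but its strength is unknown, and the R² of 0.50 to 0.61 needed for 80% power is far above what entry dose explains in that model. The shortfall comes from using a per-arm number as the total and has to be dealt with as a sample-size matter.

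**What to change.** Amend the analysis wording as follows, with covariates fixed before any comparison by arm, since the trial is open-label.

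- **Quality of life, calprotectin, CRP, ESR:** ANCOVA of the week-24 value with the baseline value as covariate. Log-transform the markers, and use rank-based ANCOVA if the residuals require it. Report the adjusted difference with its 95% CI.
- **Endoscopic response and mucosal healing:** adjust for the baseline endoscopy subscore.
- **Steroid withdrawal time:** adjust for entry steroid dose.
- **Primary outcome (optional):** a risk difference standardized over pre-specified entry dose and baseline Mayo score, with its 95% CI set against the 0.15 margin and the unadjusted difference as supportive. Standardizing keeps the result on the scale of the margin.

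First confirm in the assessment schedule that the questionnaire and the steroid dose are recorded at entry. If they are, the change costs analysis wording only. The article reports that enrolment was still under way, so the covariates could be specified in advance.

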### Outcome measures

#### Primary outcome measure

The primary outcome measure of this study is the steroid-free remission rate in patients with steroid-dependent ulcerative colitis. Remission is defined as a Mayo disease activity index score of 0–2, with no individual subscore exceeding 1 [14]. The withdrawal time of steroids will also be recorded. The outcome measure will be evaluated at the end of 24 weeks. If there is no statistical significance between the steroid-free remission rate of the TCM group and the azathioprine group, then the mean withdrawal time from steroids will be compared.

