
Chinese herbal medicine is a type of complementary and alternative medicine, and is often used in patients with inflammatory bowel disease [8], especially in China. Dai *et al.* [23] analyzed 247 patients with ulcerative colitis. The Sutherland Disease Activity Index scores for patients treated with TCM and those treated with integrated TCM and Western medicine were significantly lower for both groups after treatment (*P* < 0.01). Sugimoto *et al.* used the Chinese herbal medicine Qing-Dai to treat 20 patients with moderate ulcerative colitis. The rates of clinical response, clinical remission, and mucosal healing were 72%, 33%, and 61% at week 8, respectively [24]. Qing-Dai stimulates mucosal type 3 innate lymphoid cells to generate interleukin-22, which induces antimicrobial peptide and tight junction production, suggesting a therapeutic mechanism for mucosal healing [25]. Our study using Chinese herbal medicine plus 5-aminosalicylic in patients with steroid-dependent ulcerative colitis aims to observe improvements in the primary outcome of steroid-free remission rate, and the secondary outcomes of health-related quality of life, endoscopic response, mucosal healing, and inflammation indicators. We expect that the steroid-free remission rate of the TCM group will be improved over that of the azathioprine group. The mean withdrawal time of steroids in the TCM groups should be less than that of the azathioprine group, which would reduce the risks of steroid therapy. We anticipate that the results will show that Chinese herbal medicine is effective for patients with steroid-dependent ulcerative colitis.

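### The trial is declared and sized as noninferiority with a 15-point margin, but the stated decision rule for the primary outcome is a test of difference that never uses the margin

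*Protocol article*

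**What the plan says.** The Sample size section states "This is a noninferiority trial". It gives a margin of 0.15, "For a two-sided significance level of 0.05 and power of 80" per cent, and an azathioprine remission rate of which it says "the average rate is about 73" per cent. It concludes: "Considering a 10% loss to follow-up, the sample size is 120 cases", 60 in each group.

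The Primary outcome measure section takes steroid-free remission at 24 weeks as the primary outcome and gives one rule for acting on it: "If there is no statistical significance between the steroid-free remission rate of the TCM group and the azathioprine group", the mean time to steroid withdrawal is compared next.

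The Data management and statistical analysis section says "A chi-square test or Fisher’s exact test will be used for categorical variables". It names endoscopic response and mucosal healing as examples and sets P < 0.05 as the criterion for every analysis. Steroid-free remission appears there only under descriptive statistics.

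The Discussion adds: "We expect that the steroid-free remission rate of the TCM group will be improved over that of the azathioprine group".

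**The concern.** A noninferiority trial asks whether the new treatment can be shown to be no more than the margin worse than the control. A chi-square or Fisher test asks whether the two rates differ at all. A small trial often fails to find a difference, so a non-significant P says little about whether a loss of 15 points has been excluded.

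The article does more than leave the confidence-interval method to another document. It states a decision rule for the primary outcome, and that rule belongs to a different hypothesis from the one used for sizing. A statistical analysis plan that applied the margin would depart from the Primary outcome measure section. One that followed that section would never test what the Sample size section declares.

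At stake is the main conclusion about the herbal granules against the drug that the Background presents as recommended for these patients. Under the stated rule, a result that leaves a loss of 30 points possible would go straight on to a comparison of withdrawal times, with the noninferiority question unanswered.

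**Working it through.** **Inputs.** Margin 0.15; remission rate 0.73, taken as equal in both groups; two-sided 0.05; power 80%; 10% loss; 120 patients, 60 per group (all from the Sample size section). Difference rule: Primary outcome measure section. Tests and P < 0.05: Data management and statistical analysis section.

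**1. The plan's own sample size.** The printed formula is n = 12.365 × P(1 − P)/δ².
- 12.365 × 0.73 × 0.27 / 0.0225 = 108.3
- 108.3 × 1.1 = 119.1, rounded up to 120

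This reproduces 120 if 108.3 is taken as the total for both groups. The constant, however, is 2(1.645 + 0.842)² = 12.365, the per-group noninferiority constant at one-sided 0.05. For the stated two-sided 0.05 (one-sided 0.025) it would be 2(1.960 + 0.842)² = 15.698.

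**2. What the difference test does when TCM is worse by the full margin (58% vs 73%, 60 per group).**
- SE under no difference: √(2 × 0.655 × 0.345/60) = 0.0868
- SE under these rates: √((0.58 × 0.42 + 0.73 × 0.27)/60) = 0.0857
- P(significant) ≈ Φ((0.15 − 1.96 × 0.0868)/0.0857) = Φ(−0.235) ≈ 41%

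Exact binomial enumeration gives P(non-significant):

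| True rates, TCM vs azathioprine | Per group | Chi-square non-significant |
|---|---|---|
| 58% vs 73% | 60 | 58.8% |
| 58% vs 73% | 54 (after 10% loss) | 61.8% |
| 53% vs 73% | 60 | 37.2% |
| 73% vs 73% | 60 | 94.7% |

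In the last row, the remaining 5.3% splits equally between the two directions, so a significant result favouring TCM has probability about 2.6%.

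**3. What a margin test would do on the same data (60 per group).** Noninferiority is declared if the lower confidence limit for the difference is above −15 points. Exact enumeration:

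| True rates | 95% CI | 90% CI |
|---|---|---|
| 58% vs 73% (false declaration) | 2.5% | 5.1% |
| 73% vs 73% (power) | 46% | 58% |

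Wald and score limits agree to within 0.2 percentage points in every cell. By formula, SE = √(2 × 0.1971/60) = 0.0811 and 0.15/0.0811 = 1.851. Power is then Φ(1.851 − 1.960) = 46%, or Φ(1.851 − 1.645) = 58%. With 54 per group the same formula gives 42% and 54%.

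**4. Two possible results at 60 per group (Wald limits).**
- 35/60 vs 44/60: the difference is exactly −15 points, chi-square P = 0.083, Fisher P = 0.123, 95% CI −31.8 to +1.8. There is no significant difference, and noninferiority clearly fails.
- 44/60 vs 44/60: P = 1.0; 95% CI −15.8 to +15.8, 90% CI −13.3 to +13.3. Identical observed rates miss the margin at 95% and meet it at 90%, so the confidence level has to be fixed in advance.

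**The case against.** Five objections deserve an answer.

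- **The chi-square sentence names only secondary outcomes as examples.** This is correct, and difference tests for secondary outcomes do not conflict with a noninferiority primary. That sentence reaches the primary outcome only because remission is categorical. The point therefore rests mainly on the Primary outcome measure section, where the difference rule is attached to the primary outcome directly.
- **A condensed article may leave the margin test to an analysis plan that is not shown.** The absence of a confidence-interval method would not be a finding on its own. The stated rule that conflicts with the declared design is one.
- **A reader might infer that a non-significant P will be reported as noninferior or comparable to azathioprine, and so that the plan has a 59% false-claim rate.** The article does not say this. It says only that withdrawal time is then compared, and it describes the findings as a basis for confirmatory studies. The 59% is the probability of a non-significant test. It becomes an error rate only under that unstated reading.
- **A reader might infer that the plan can never show noninferiority.** That is too strong. A significant result favouring TCM would imply it, improbable as that is under the sizing assumptions. The collected data would also allow the margin to be applied.
- **The Discussion's expectation of improvement might look like a competing superiority hypothesis.** It is only an expectation and is compatible with a noninferiority design.

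None of this removes the conflict between the declared design and the rule for the primary outcome.

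**Conclusion.** The point holds as a contradiction within the article. The design is noninferiority with a 15-point margin. The only decision rule given for the primary outcome, and the general P < 0.05 criterion, test for a difference and never use the margin. Apart from the one-sided exception above, a result reached by these rules does not answer the trial's question. It must be corrected, because the primary conclusion depends on it.

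The figures assume a 73% azathioprine rate, independent binomial outcomes, an uncorrected chi-square test and 60 analysed per group. The 2.5% error also assumes a 95% CI, which matches the stated two-sided 0.05. The sample-size constant matches a 90% CI instead, and the article does not reconcile the two.

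**What to change.** - In the analysis section, define the primary analysis as the risk difference (TCM minus azathioprine) in week-24 steroid-free remission with a two-sided 95% score CI (Miettinen-Nurminen or Farrington-Manning). Declare noninferiority only if the lower limit is above −15 points. Test superiority only after noninferiority is shown.
- In the Primary outcome measure section, replace the absence of statistical significance as the branch for the primary outcome, and state the role of withdrawal time separately.
- The Discussion's expectation can stay.
- Restate the power, and reconcile the constant 12.365 (one-sided 0.05) with the stated two-sided 0.05.

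The wording costs a few sentences and needs no new data. Since the trial is open-label and enrolling, date the change before outcomes are compared by group.

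The rewording does not restore 80% power. At 73% in both groups, 80% needs 109 per group at one-sided 0.05 (218 in total; 109/0.9 rounds up to 122 per group, 244 with loss). At one-sided 0.025 it needs 138 per group (276; 138/0.9 rounds up to 154, 308 with loss). If 120 is kept, the protocol should say that power is about 46% with a 95% CI, or 58% with a 90% CI, before any loss.

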## Discussion

Ulcerative colitis is a chronic inflammatory bowel disease characterized by a relapsing-remitting course owing to recurrent intestinal inflammation. Steroids are often prescribed for moderate to severe ulcerative colitis patients. Although steroids are usually effective, long-term steroid use should be avoided because of its severe side effects. Patients who initially respond to steroids but then relapse after tapering or shortly after discontinuation, and require reintroduction of steroids to induce remission are defined as steroid dependent. The therapeutic objective of steroid-dependent patients is to achieve steroid-free remission.

In view of the side effects of steroids, different drugs are used in the management of steroid-dependent ulcerative colitis. Drugs used include established agents, such as thiopurines, methotrexate, infliximab, adalimumab, vedolizumab, and golimumab. If common treatments fail, colectomy may be performed [16]. Current guidelines recommend thiopurines as first-line therapy to spare steroids in steroid-dependent ulcerative colitis [3, 6]. Therefore, the thiopurine agents azathioprine and 6-mercaptopurine are used to sustain steroid withdrawal in patients with steroid-dependent ulcerative colitis [5]. Azathioprine is a purine analog that competitively inhibits the biosynthesis of purine ribonucleotides [17]. Azathioprine is the main therapy for steroid-dependent patients in China, because vedolizumab and golimumab are not available, and adalimumab is not indicated for use in patients with ulcerative colitis. Furthermore, cessation of infliximab is still considered in clinical practice because of its high cost and fear of long-term side effects [18]. There is also a reduced response to infliximab, which may reach approximately 13% per year with uninterrupted scheduled maintenance therapy [19]. Fraser *et al.* reported that the remission rate was 87% in 346 ulcerative colitis patients who received more than 6 months of azathioprine treatment [10]. Another study demonstrated that the steroid-free remission rate was 59.1% in patients with steroid-dependent or steroid-resistant ulcerative colitis treated with azathioprine [9]. The most common adverse event of azathioprine is leukopenia, which occurs in 3.8% of patients [20]. Other adverse events include hepatitis, infection, pancreatitis, and hair loss. Once absorbed into the plasma, azathioprine is nonenzymatically converted to 6-mercaptopurine. 6-Mercaptopurine can be metabolized to 6-methylmercaptopurine by the enzyme thiopurine methyltransferase (TPMT), to 6-thiouric acid by the enzyme xanthine oxidase, and to the active metabolites of 6-thioguanine nucleotide. 6-Thioguanine nucleotide is the active ribonucleotide of 6-mercaptopurine; it functions as a purine antagonist, resulting in immunosuppression and lymphocytotoxicity. A deficiency in TPMT may lead to preferential 6-mercaptopurine metabolism into 6-thioguanine nucleotide, resulting in myelosuppression [21]. An apparent genetic polymorphism of TPMT is associated with TPMT enzyme deficiency. Despite a lower frequency of variant TPMT observed in Asian populations [22], lower starting doses of azathioprine are recommended in Asian populations than in white populations, along with close monitoring of complete blood count and liver function [13].

Chinese herbal medicine is a type of complementary and alternative medicine, and is often used in patients with inflammatory bowel disease [8], especially in China. Dai *et al.* [23] analyzed 247 patients with ulcerative colitis. The Sutherland Disease Activity Index scores for patients treated with TCM and those treated with integrated TCM and Western medicine were significantly lower for both groups after treatment (*P* < 0.01). Sugimoto *et al.* used the Chinese herbal medicine Qing-Dai to treat 20 patients with moderate ulcerative colitis. The rates of clinical response, clinical remission, and mucosal healing were 72%, 33%, and 61% at week 8, respectively [24]. Qing-Dai stimulates mucosal type 3 innate lymphoid cells to generate interleukin-22, which induces antimicrobial peptide and tight junction production, suggesting a therapeutic mechanism for mucosal healing [25]. Our study using Chinese herbal medicine plus 5-aminosalicylic in patients with steroid-dependent ulcerative colitis aims to observe improvements in the primary outcome of steroid-free remission rate, and the secondary outcomes of health-related quality of life, endoscopic response, mucosal healing, and inflammation indicators. We expect that the steroid-free remission rate of the TCM group will be improved over that of the azathioprine group. The mean withdrawal time of steroids in the TCM groups should be less than that of the azathioprine group, which would reduce the risks of steroid therapy. We anticipate that the results will show that Chinese herbal medicine is effective for patients with steroid-dependent ulcerative colitis.

There are several limitations to our study. First, this is an open-label randomized controlled trial without double blinding. Because of the lack of placebo control groups, our findings will be interpreted with caution. Another limitation to this study is the lack of TPMT and 6-thioguanine nucleotide testing. Some patients do not respond to azathioprine because of lower 6-thioguanine nucleotide levels. Although a lower frequency of variant TPMT is observed in Asian populations, TPMT and 6-thioguanine nucleotide testing may assist dose optimization of azathioprine to achieve response and avoid drug-induced toxicity. Both TPMT and 6-thioguanine nucleotide testing will be determined in corollary studies. The last limitation is of first-choice therapy in steroid-dependent ulcerative colitis. The Toronto consensus in 2015 recommends anti-TNF therapy to induce and maintain complete steroid-free remission in patients with steroid-dependent ulcerative colitis [26]. The consensus group also recommends that anti-TNF plus azathioprine therapy is the preferred choice for steroid-dependent patients rather than monotherapy to induce complete remission [26, 27]. However, azathioprine is still the most practicable therapy for steroid-dependent patients in China, because anti-TNF agents are not widely used. Combination therapy with anti-TNF agents will be available in the future. Notwithstanding its limitations, this study will suggest whether Chinese herbal medicine can be an effective complementary and alternative medicine in patients with steroid-dependent ulcerative colitis.

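### In this open-label trial, no stated safeguard covers the grading of the Mayo endoscopy subscore, which can decide the primary outcome and defines two secondary ones

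*Protocol article*

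**What the plan says.** The limitations paragraph of the Discussion states that "this is an open-label randomized controlled trial without double blinding", and adds that findings will be read cautiously because there is no placebo group.

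Under Primary outcome measure, steroid-free remission at 24 weeks requires a total Mayo score of 0 to 2 "with no individual subscore exceeding 1". Secondary outcome measures makes clear that endoscopy is one of those subscores. Endoscopic response is a fall of at least 1 from baseline in that subscore, and mucosal healing is a subscore of 0 or 1.

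Two sections describe protection against bias. Randomization gives the sequence to an independent person outside observation and assessment, and keeps the researchers blind to the sequence. Data management and statistical analysis assigns the analysis to an independent statistician. Neither mentions who grades the endoscopy or what that person knows.

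Sample size says "This is a noninferiority trial" with a margin of 0.15. The Discussion says "We expect that the steroid-free remission rate of the TCM group will be improved over that of the azathioprine group".

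**The concern.** The Mayo endoscopy grade is a visual judgement, and it can tip the primary outcome. The article takes up blinding and lists its measures, but they stop at the sequence and the analysis. Concealing the sequence protects who enters which arm. It does not protect an outcome graded 24 weeks later, when the treatment may be known. An independent statistician analyses whatever grades are recorded.

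In a noninferiority comparison, generous grading in the new arm pushes toward the claim the trial is set up to test. The same grade feeds two secondary outcomes, so any bias would appear in all three and could look like corroboration.

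**Working it through.** **1. When does the endoscopy grade decide remission?** The patient must be off steroids, with a total of at most 2 and every subscore at most 1.
- Grade 2 read as 1 turns failure into success only if the other subscores sum to at most 1. The total is then at most 1 + 1 = 2.
- Grade 1 read as 0 does so only if the other subscores sum to exactly 2, each at most 1. The total falls from 3 to 2.
- In all other patients a one-grade shift leaves the primary outcome unchanged.

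**2. Inputs from the protocol article.** Sample size gives the 0.15 margin, the expected rate ("the average rate is about 73" percent) and the error rates ("For a two-sided significance level of 0.05 and power of 80" percent). Methods/Design gives 60 per group. The printed formula yields 12.365 × 0.73 × 0.27 / 0.15² = 108.3, and 108.3 / 0.9 = 120.4. The stated 120 is therefore matched only if the formula's result is read as a total. That is a separate matter; 60 per group is taken here as planned.

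**3. Assumptions, not in the article.**
- Noninferiority is declared if the Wald lower limit exceeds −0.15: p_T − p_C − z·√[(p_T(1−p_T) + p_C(1−p_C))/60] > −0.15. The analysis section names only chi-square or Fisher tests for categorical outcomes.
- The true rates sit exactly at the margin: 73% on azathioprine, 58% on TCM.
- A net k gradings favour TCM, so its recorded rate is 0.58 + k/60. For k = 3 this adds 3/60 = 5 points, one third of the margin.

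**4. Chance of wrongly declaring noninferiority** (exact enumeration over both binomial counts):

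| Net gradings favouring TCM | z = 1.96 | z = 1.645 |
|---|---|---|
| 0 | 2.5% | 5.1% |
| 3 | 8.6% | 14.5% |
| 6 | 22.8% | 32.8% |

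Adding k as a fixed count instead gives 8.9% and 23.6% at z = 1.96, so the modelling choice matters little.

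**5. Equal leniency.** Raising both rates by k/60 leaves the error at about 2.6% for k = 3 and for k = 6 (z = 1.96). Only a difference between arms matters.

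**6. Single results** (azathioprine 44/60, z = 1.96):
- TCM 44/60: 0 − 1.96 × 0.0807 = −0.158, fails.
- TCM 45/60: 0.0167 − 1.96 × 0.0799 = −0.140, passes.
- TCM 35/60: −0.15 − 1.96 × 0.0855 = −0.318, fails; reaching 45 takes 10 changed gradings.

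One grading can therefore decide a result at the boundary, but a few cannot rescue an observed 15-point deficit.

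**The case against.** The strongest objection is that this rests on silence. Open-label describes treatment masking and is compatible with a masked assessor. The article refers to an overview of assessments and a SPIRIT checklist (Additional files 1 and 2), which are not shown, and a condensed article may leave grading arrangements to the full protocol. This stands to the extent that a reader might infer that the graders are known to be unmasked, and the document does not establish that. It also does not say who performs the endoscopy. What remains is narrower: the article sets out its safeguards and its open-label limitation, and none reaches the grading of its primary outcome.

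A reader might also infer that a few gradings would create noninferiority. They would not in general. Under the illustration, about 91% of trials with 3 favourable gradings and 77% with 6 still fail. The number and direction of the gradings have no source in the article. The authors' expectation that TCM will do better is a hypothesis, not evidence of biased grading; it only makes one direction more plausible.

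The limitation is disclosed, and the Abstract presents the findings as a basis for confirmatory studies. That is fair, but disclosure does not reduce bias where a simple measure could.

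Finally, masking the endoscopy is a partial remedy. The other Mayo components, and the judgement of clinical remission that starts steroid tapering (Basic treatment), stay open. This stands in full.

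**Conclusion.** The point holds in a limited form. As written, the plan leaves a subjective component of the primary outcome, which also defines two secondary outcomes, without a stated safeguard against differential grading. The premises about the outcome definition, the open label and the scope of the safeguards are all in the article. The absence of masked grading is inferred from what it omits.

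The figures of 8.6% and 23% against 2.5% show sensitivity; they do not estimate the bias in this trial. They depend on the assumed decision rule, a true deficit equal to the margin, and all net misgrading favouring TCM. With equal leniency there is essentially no inflation. The change is worth making because it is cheap, not because bias has been shown.

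**What to change.** Add to Primary outcome measure and Secondary outcome measures that, for all remaining assessments:
- whoever already performs the endoscopy at the site records the Mayo endoscopy subscore at the procedure, without being told the allocation;
- the request form does not show the arm, and patients are asked not to disclose it;
- the case report form records whether masking held.

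If masked grading is already in place, a sentence saying so is enough.

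Also state in the limitations that the other Mayo components and the tapering decision are made open-label.

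**Cost:** an instruction to sites, a revised request form and one case report form field, with no added reader or procedure. There is some minor logistics, and masking will be imperfect. Trial status reports the first enrolment on 24 April 2015, with recruitment continuing, so if earlier gradings were unmasked the data will mix both kinds. The case report form field lets the two be told apart.
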